### End points

In total, patients will be followed for 5 years after surgery. The primary end point of the study is postoperative surgical recurrence. Surgical recurrence is defined as the requirement for repeat surgery for a CD-related indication caused by recurrent disease in the same anatomical areas. If reoperation is required it should be documented whether the reason is a specific CD-related complication, or a complication related to surgery in general (i.e., hemorrhage, intraperitoneal collection not amenable to conservative treatment, wound dehiscence, anastomotic leakage). CD-related indications for surgery include: (1) development of symptoms refractory to medical treatment; and (2) development of a complication caused by CD (i.e., fistula, perforation, and obstruction).

Secondary end points include assessment of endoscopic recurrence and clinical recurrence. Endoscopic recurrence will be assessed using the widely accepted Rutgeert’s score [15]. Only disease (Rutgeert’s score i2, or higher) proximal to the anastomosis or in the perianastomotic area is considered to be consistent with endoscopic recurrence. Disease in other sites will not be considered to be recurrence. Clinical recurrence is defined as the presence of endoscopic disease or radiological evidence plus the presence of symptoms attributable to CD that are severe enough to require medical or surgical treatment.

In addition, intra-operative complications and 30-day postoperative outcomes will be evaluated. These include estimated blood loss, duration of surgery, postoperative morbidity, reoperation rate, and the length of postoperative hospital stay. Postoperative complications will be recorded and classified based on the Clavien-Dindo classification [16].

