### Statistical analysis

Data will be presented as median (range), mean, and standard deviation for continuous variables, and percentages for categorical and ordinal data. In order to test whether there are differences between the two groups in the reduction of the primary and secondary outcome, Student’s *t* tests will be performed for continuous variables and chi-square or Fisher’s exact test for categorical variables. Those variables in which statistically significant differences are found will be introduced in the analyses as covariates. Kaplan-Meier analysis with log-rank statistics will be used to assess event-free interval and Cox forward conditional proportional hazards for regression analysis. We plan intention-to-treat analysis of the primary outcome. The full analysis set and per-protocol set will be used for the assessment of efficacy. Interim analyses will be done annually for the first 5 years after index surgery, and the sample size would be adjusted accordingly. An interim analyses will be performed to see if the trial should be continued or stopped, and so it serves as a safeguard. If the outcomes are very poor, more than would be expected, a clear-cut trend towards increased severe morbidity (classed as Clavien-Dindo grade 3 or greater) in relation to either the control or test group, the trial would be stopped and the enrolled participants would have been followed for outcomes and the primary analysis would have focused on the mortality end point. Alternatively, if there was a clear difference between the two groups in terms of benefits for the test cohort, with statistically significant findings emerging on comparison of one group over another that support uncontestable differences between groups, then it might also be stopped and all enrolled participants will be followed for outcomes and the primary analysis will focus on the efficacy end point. Data will be monitored by the treating clinicians and external independent trial monitoring committee, and the principle investigator of each participative site will take overall responsibility. An external independent trial monitoring committee will also analyze interim anonymized outcome data. All analyses considered a *P* value of ≤ 0.05 as statistically significant.

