### Cessation of trial

The trial will stop in three circumstances: (1) once 5 years after first enrollment has been reached; (2) statistically significant findings emerge on comparison of one group over another that support uncontestable differences between groups; and (3) a clear-cut trend is demonstrated toward increasingly severe morbidity (classified as Clavien-Dindo grade 3 or greater) in either treatment arm.

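### After a stop for harm, the primary analysis is assigned to a mortality end point that the protocol never defines, while the trigger for that stop is severe morbidity

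*Protocol article*

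**What the plan says.** All references are to the protocol article.

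- **End points.** "The primary end point of the study is postoperative surgical recurrence". On the next tier, "Secondary end points include assessment of endoscopic recurrence and clinical recurrence". Intra-operative and 30-day outcomes follow: "These include estimated blood loss, duration of surgery, postoperative morbidity, reoperation rate, and the length of postoperative hospital stay". On grading, "Postoperative complications will be recorded and classified based on the Clavien-Dindo classification".
- **Statistical analysis, harm branch.** The trigger is "a clear-cut trend towards increased severe morbidity (classed as Clavien-Dindo grade 3 or greater) in relation to either the control or test group". After such a stop, enrolled participants are followed for outcomes and "the primary analysis would have focused on the mortality end point".
- **Statistical analysis, benefit branch.** After a stop for benefit, "the primary analysis will focus on the efficacy end point".
- **Cessation of trial.** The third stopping circumstance is that "a clear-cut trend is demonstrated toward increasingly severe morbidity (classified as Clavien-Dindo grade 3 or greater) in either treatment arm". Deaths are not mentioned.

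The Abstract and the Discussion also give surgical recurrence as the primary end point. Neither mentions mortality.

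**The concern.** The harm branch refers to a mortality end point as if it were already defined, and it is not. It has no definition, no time window and no place in the list of end points, although follow-up runs for 5 years. The branch is also entered on one outcome (severe morbidity) and then analysed primarily on another (death).

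The clause matters only if the trial is stopped for harm, but that is when the reader most needs a clear primary result. In a trial of 116 patients a comparison of deaths is likely to rest on very few events. A trial closed because of excess severe complications could then carry a headline result of no difference, and the monitoring committee would have to guess what the clause intended.

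**Working it through.** The main check is textual. A short calculation then shows what the clause would mean if followed literally. The plan states no figure on this point, so there is none to reproduce.

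**1. Is there a mortality end point?**

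| Place | Outcome named |
|---|---|
| Abstract (Methods), End points, Discussion: primary | Surgical recurrence |
| Abstract (Methods), End points: secondary | Endoscopic and clinical recurrence |
| End points: intra-operative and 30-day | Blood loss, duration of surgery, morbidity (Clavien-Dindo), reoperation, length of stay |
| Statistical analysis: harm trigger | Clavien-Dindo grade 3 or greater morbidity |
| Cessation of trial: harm trigger | Clavien-Dindo grade 3 or greater morbidity |
| Statistical analysis: analysis after a harm stop | Mortality |
| Statistical analysis: analysis after a benefit stop | The efficacy end point |

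Mortality appears in one row only. The benefit branch points to something the trial has; the harm branch does not. Deaths would be captured only as part of complication grading.

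**2. How many deaths might there be?** Inputs: 116 patients (Sample size), taken as 58 per arm. The documents give no death rate, so 0 to 1% per arm is an assumption.

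- Expected deaths: 116 × 0 = 0, up to 116 × 0.01 = 1.16, so about 0 to 1.

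**3. What split of deaths would be significant?** The plan's threshold is P ≤ 0.05. With equal arms and all deaths in one arm, the two-sided Fisher P for k deaths is 2 × C(58,k) / C(116,k).

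- k = 5: C(58,5) = 4,582,116 and C(116,5) = 160,389,488. P = 2 × 4,582,116 / 160,389,488 = 0.057, which misses the threshold.
- k = 6: the one-sided ratio for k = 5, 0.02857, is multiplied by 53/111, giving 0.01364. P = 2 × 0.01364 = 0.027, which meets it.

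So at least six deaths against none would be needed, when about 0 to 1 in total are expected under the assumption.

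**4. Power under other assumed death rates** (58 per arm, two-sided 5%, pooled normal approximation for two proportions):

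| Assumed rates | Power |
|---|---|
| 1% vs 2% | about 6% |
| 0.5% vs 2% | about 11% |
| 1% vs 5% | about 24% |

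These use the full 116 patients. A harm stop during enrolment would leave fewer.

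**The case against.** **It may be a slip.** The sentence's own trigger is morbidity, Cessation of trial repeats it, and the natural counterpart of an efficacy end point is a safety or morbidity end point. *Mortality* may simply be a misprint for *morbidity*. This is plausible, and the article cannot settle it. Either way the printed rule names the wrong outcome and needs correcting. Nor is it a detail left to a fuller document, because it is a positive statement that conflicts with other sections of the same article.

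**Stronger readings that the article does not support.**

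- *A trial stopped for harm could conclude nothing.* Enrolled participants are still followed, complications are still graded, and intention-to-treat analysis of the primary outcome is still planned. Morbidity and recurrence would be reported; only the result labelled primary would be uninformative.
- *The end point is switched after seeing the data.* The branch is written down in advance. It is a badly matched contingency, not an after-the-fact change, and the mismatch is the better criticism.
- *Deaths go unrecorded.* They can be captured through complication grading. What is missing is mortality as a defined end point.
- *Surgical recurrence is formally demoted.* The clause says where the primary analysis would focus, while End points still defines recurrence as primary. The two are left unreconciled.

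**The arithmetic depends on choices.** The plan allows chi-square or Fisher's exact test. Uncorrected chi-square for 0/58 versus 5/58 gives 116 × (58 × 5)² / (58 × 58 × 5 × 111) = 5.2, P about 0.02. With an expected 2.5 deaths per arm, Fisher's is the appropriate choice of the two. The death rate remains an assumption. The textual conflict depends on neither.

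**Conclusion.** The point holds as a conflict in the printed text. The analysis after a harm stop is assigned to an end point that is not defined, and it differs from the outcome that triggers the stop.

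The size of the consequence is conditional. At an assumed 0 to 1% mortality per arm, with 58 per arm and Fisher's test, the comparison labelled primary would very likely show no difference. Even the 1% versus 5% scenario gives power of only about 24%. The clause operates only after a stop for harm. It affects neither the sample size nor the main analysis of a trial that runs to its planned end. It should be corrected, since the repair is small and the branch is meant as a safeguard.

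**What to change.** Reconcile End points, Statistical analysis and Cessation of trial by replacing the mortality clause. Suggested wording:

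*If the trial is stopped for harm, all enrolled participants remain in follow-up. Surgical recurrence, analysed by intention to treat, remains the primary end point. The safety conclusion rests on the proportion of patients in each arm with Clavien-Dindo grade 3 or greater morbidity, deaths included, reported as a risk difference with its 95% confidence interval.*

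If the sponsor did intend mortality, it needs a definition, a time window and a stated role under End points, with a reason for using it after a stop triggered by morbidity.

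The stopping trigger is not changed. The cost is one sentence, and the complication data are already to be collected under End points.

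### Annual efficacy looks tied to statistical significance at P ≤ 0.05 do not hold the 5% error rate, and the two stopping passages conflict on force and direction

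*Protocol article*

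**What the plan says.** All places are in the protocol article.

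- **Looks (Statistical analysis).** "Interim analyses will be done annually for the first 5 years after index surgery, and the sample size would be adjusted accordingly".
- **Efficacy stop (Statistical analysis).** The trigger is a clear difference in benefit for the test cohort, "with statistically significant findings emerging on comparison of one group over another that support uncontestable differences between groups". The consequence is permissive: "then it might also be stopped and all enrolled participants will be followed for outcomes".
- **Threshold (Statistical analysis).** The section closes by applying to all analyses a "value of ≤ 0.05 as statistically significant", with no exception for interim looks.
- **Efficacy stop (Cessation of trial).** "The trial will stop in three circumstances", one of which is that "statistically significant findings emerge on comparison of one group over another that support uncontestable differences between groups". No direction is given.
- **Monitoring (Statistical analysis).** "Data will be monitored by the treating clinicians and external independent trial monitoring committee". The section adds that the committee will analyse anonymized interim outcome data.
- **Error rate (Sample size).** 80% power and 5% significance for a fall of 20 points from 30%, with no allowance for repeated looks.

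**The concern.** A 5% significance level holds for one test. Here the same comparison is to be made up to five times on accumulating data, a significant result can end the trial, and the only definition of significant is P ≤ 0.05 each time. Chance then has several opportunities to produce a positive finding. At stake is the error rate of the main conclusion, in a trial whose Discussion says a positive result may set a new surgical standard.

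There is also a contradiction. A committee following the analysis section has discretion and looks for benefit of extensive excision. A committee following Cessation of trial must stop, whichever arm is ahead. The two rules have different error rates, and the plan does not say which governs.

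**Working it through.** **1. The plan's own figures.** For 30% versus 10% with 80% power, n per arm = [z_α·√(2p̄(1−p̄)) + z_β·√(p₁q₁ + p₂q₂)]² / (p₁ − p₂)², with p̄ = 0.20.

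- One-sided 5%: (1.645 × 0.5657 + 0.8416 × 0.5477)² / 0.04 = 48.4, so 49 per arm and 98 in total. This is close to the stated 100.
- Two-sided 5%: (1.960 × 0.5657 + 0.8416 × 0.5477)² / 0.04 = 61.6, so 62 per arm and 124 in total.

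The stated size therefore fits one look at a one-sided 5% level. Sidedness is not stated, so both are considered below.

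**2. General result.** With k equally spaced looks, Z_k = (X₁ + … + X_k)/√k, where the X are independent standard normal under the null. The overall error is the probability that |Z| ≥ 1.96 at any look (2,000,000 simulated trials).

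| Looks | 1 | 2 | 3 | 4 | 5 | 6 |
|---|---|---|---|---|---|---|
| Overall error | 5.0% | 8.3% | 10.8% | 12.6% | 14.2% | 15.5% |

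One look returns the nominal 5%. Five looks at one-sided 0.05 give 13.0%. Spacing the information as yearly per-patient follow-up would gives 13.9%.

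**3. Expected events in this trial.** Inputs: N = 116, enrolment 1 February 2019 to 31 December 2020 (23 months), 30% at 60 months in both arms. Assumptions: uniform accrual, constant hazard, no loss to follow-up, looks 12 to 60 months after first enrolment. The monthly hazard is λ = −ln(0.70)/60 = 0.00594.

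- Month 12: 116/23 × [12 − (1 − e^(−12λ))/λ] = 116/23 × 0.419 ≈ 2.
- Later month T: 116 × [1 − (e^(−(T−23)λ) − e^(−Tλ))/(23λ)], giving about 8, 16, 23 and 29.

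**4. Error rate in this trial.** Probability of at least one P ≤ 0.05 over the five looks under the null:

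| Test | Overall error |
|---|---|
| Log-rank | 13.5% |
| Chi-square | 14.5% |
| Fisher's test when expected counts are small, otherwise chi-square | 12.6% |
| Fisher's test at every look | 7.3% |
| Benefit direction alone (nominal 2.5%) | 6.9% |

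Repeat runs differ by about half a point (log-rank 12.9–13.8% for five-year rates of 20% or 30%; mixed Fisher/chi-square 12.1%). Normal theory gives 16.0% for calendar looks at a 20% five-year rate, but it overstates the error when early looks hold very few events; the simulated log-rank figure there is 12.9%.

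**5. Boundaries that restore 5% over five equal looks.** P < 0.001 at four interims and 0.05 at the end gives 5.1%; lowering the final level by 0.001 to 0.049 brings this to about 5.0%. O'Brien-Fleming nominal levels of 0.000005, 0.0013, 0.0084, 0.0226 and 0.0414 give 5.0%.

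**6. Sample-size adjustment.** On calendar-year looks, only the first precedes the end of enrolment, with about 2 events expected. If a look instead waits for every patient to reach each anniversary, none precedes it.

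**The case against.** *The rule asks for more than P ≤ 0.05.* It does: the difference must be clear and uncontestable, and the analysis section says only that the trial might stop. A reader could infer that 14% is this trial's false-positive rate. The documents do not support that as a flat statement, because the figure assumes that every P ≤ 0.05 counts as a positive result. It also depends on the test, and the plan names several. What stands is that neither qualifier has a number, Cessation of trial drops *might*, and inflation remains under every test examined.

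*Boundaries belong in an analysis plan or committee charter not shown.* Their absence alone would be no finding. But the protocol sets one threshold for all analyses, so a stricter interim boundary elsewhere would contradict it.

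*Early stops would exaggerate the effect.* This is tempting, but the plan keeps following all enrolled participants after such a stop, and on calendar looks enrolment is closed before the second one. If the primary analysis uses the completed follow-up, exaggeration is reduced, as is the inflation. The text does not say whether that later analysis replaces the interim result.

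*Secondary end points could trigger the stop.* No end point is named in the trigger, but the same passage refers to a single efficacy end point, and Follow-up calls surgical recurrence the primary and ultimate one. Stopping on endoscopic recurrence is a possible reading, not a stated rule.

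*Interim trends would reach treating clinicians.* The plan says they monitor data, not that they see results by arm, and it gives anonymized interim outcome data to the independent committee. Leakage is not established; only the lack of clarity is.

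**Conclusion.** Wrong as written. Annual comparative looks, stopping tied to statistical significance, and P ≤ 0.05 for all analyses cannot together deliver the 5% in Sample size. If every P ≤ 0.05 is treated as a positive result, the overall two-sided error is about 12–14% under the log-rank test, chi-square, or Fisher's test for small expected counts. It is about 7% with Fisher's test throughout, and about 7% against 2.5% for benefit alone. These figures rest on five looks and on the accrual and hazard assumptions shown. An undisclosed stricter reading of *uncontestable* would lower them, but the protocol supplies none.

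Separately, and without any calculation, Statistical analysis and Cessation of trial disagree on whether stopping is optional and whether it applies in one direction or both. They must be reconciled.

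**What to change.** - **One efficacy rule, in the same words in both sections.** State that efficacy stopping applies only to surgical recurrence, by intention to treat, with one named test, and only across a group-sequential boundary. Examples are P < 0.001 at each interim and about 0.049 at the final analysis, or an O'Brien-Fleming-type spending function on events. Give the sidedness, the direction, and whether crossing is binding.
- **Threshold.** Exempt interim looks from the general P ≤ 0.05.
- **Sample-size adjustment.** Delete the clause, or limit it to one review of the pooled, blinded event rate before accrual closes.
- **Access.** State that by-arm interim results go only to the independent committee, since the text leaves unclear what the treating clinicians see.

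The cost is a wording amendment, about 0.001 of alpha at the final analysis with the first boundary (a final level near 0.041 with the five-look O'Brien-Fleming boundary above), and a harder early stop for benefit.

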### Cessation of trial

The trial will stop in three circumstances: (1) once 5 years after first enrollment has been reached; (2) statistically significant findings emerge on comparison of one group over another that support uncontestable differences between groups; and (3) a clear-cut trend is demonstrated toward increasingly severe morbidity (classified as Clavien-Dindo grade 3 or greater) in either treatment arm.

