### Sample size

There are no registered or published randomized controlled trials (RCTs) comparing limited with extensive mesenteric resection in patients with CD. Our sample size calculation is based on the surgical recurrence in a retrospective study reported by Coffey et al. [9]. It is estimated that 30% of subjects undergoing an ileocolonic anastomosis with conventional limited mesenteric excision would develop surgical recurrence at 60 months after surgery. To detect a 20% decrease in the surgical recurrence rate after wide mesenteric excision with 80% power and 5% significance, a total of 100 patients must be recruited. The sample size is adjusted to 116 to allow for a 10% loss to follow-up and 5% anastomotic leak.

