### Trial status

The protocol reported here is version 1.2, dated 30 October 2018. Trial enrollment began on 1 February 2019 and is anticipated to finish on 31 December 2020.

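### Stopping five years after the first enrollment contradicts the promised five-year follow-up of patients and the 60-month risk used for the sample size

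*Protocol article*

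**What the plan says.** Four places in the protocol article bear on how long patients are observed.

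- **Cessation of trial** lists three circumstances in which the trial stops. The first is "once 5 years after first enrollment has been reached".
- **End points**: "In total, patients will be followed for 5 years after surgery".
- **Sample size** assumes that 30% of patients with limited excision "would develop surgical recurrence at 60 months after surgery". It plans "To detect a 20% decrease in the surgical recurrence rate after wide mesenteric excision" and arrives at 100 patients for 80% power at the 5% level. That number is inflated to 116 for loss to follow-up and anastomotic leak.
- **Trial status**: "Trial enrollment began on 1 February 2019 and is anticipated to finish on 31 December 2020".

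The Statistical analysis section also counts its annual interim looks over five years from index surgery. For the outcome itself it says "Kaplan-Meier analysis with log-rank statistics will be used to assess event-free interval".

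**The concern.** End points, Sample size and the interim schedule all run the clock from each patient's operation. The first stopping circumstance runs it from the first enrollment in the trial. The two agree only if everyone is operated on at the start, and the planned accrual lasts almost two years. Sites that follow Cessation of trial would close late entrants well before End points allows. Any reoperations in the missing months would go unrecorded and could not be recovered later. The trial would then run with fewer primary events than its sample size assumes.

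**Working it through.** **Reproducing the plan's figure.** The 20% decrease must be absolute (30% versus 10%), because a relative 20% (30% versus 24%) would need 1,352 patients or more. The pooled two-proportion formula without continuity correction is n per arm = [z_α√(2p̄q̄) + z_β√(p₁q₁ + p₂q₂)]² / (p₁ − p₂)², with p̄ = 0.20:

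- one-sided 5%: (1.645 × 0.5657 + 0.8416 × 0.5477)² / 0.04 = 48.4, so 49 per arm and 98 in total, close to the stated 100;
- two-sided 5%: (1.960 × 0.5657 + 0.8416 × 0.5477)² / 0.04 = 61.6, so 62 per arm and 124 in total.

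Inflation: 100 × 1.10 × 1.05 = 115.5, which rounds up to the stated 116.

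**Calendar.** Dates are from Trial status. I take surgery as occurring at enrollment; any delay shortens follow-up further.

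- Accrual, 1 Feb 2019 to 31 Dec 2020: 699 days / 30.4375 = 22.97 months.
- Stop, five years after 1 Feb 2019: 1 Feb 2024.
- Last entrant, 31 Dec 2020 to 1 Feb 2024: 1,127 days / 30.4375 = 37.03 months.
- Mean follow-up under uniform accrual: 60 − 22.97/2 = 48.5 months (4.04 years).
- Five years for the last entrant would end on 31 Dec 2025, about 83 months after first enrollment.

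**Expected risks at the stop.** Uniform accrual, constant hazards and 1:1 allocation are assumptions; the article gives none of them.

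- Hazards per month: −ln(0.7)/60 = 0.005945 and −ln(0.9)/60 = 0.001756. Hazard ratio: ln(0.9)/ln(0.7) = 0.295.
- Mean risk over follow-up uniform on a = 37.03 to b = 60 months: 1 − (e^(−λa) − e^(−λb)) / [λ(b − a)].
- Limited excision: 1 − (0.8024 − 0.7000)/0.1365 = 25.0%.
- Extensive excision: 1 − (0.9370 − 0.9000)/0.0403 = 8.2%.
- Events per 100 patients: 50 × (0.250 + 0.082) = 16.6, against 50 × (0.30 + 0.10) = 20, which is 17% fewer.

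**Power at 50 per arm, no attrition.** The Schoenfeld approximation is Φ(½√d × |ln HR| − z_α), with |ln HR| = 1.219. The log-rank simulation used 40,000 runs per scenario.

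| Method | Sides | All followed 60 months | Stop on 1 Feb 2024 |
|---|---|---|---|
| Log-rank, simulated | two | 73% | 64% |
| Log-rank, simulated | one | 83% | 76% |
| Log-rank, Schoenfeld | two | 78% | 70% |
| Log-rank, Schoenfeld | one | 86% | 80% |
| Two proportions | two | 71% | 62% |
| Two proportions | one | 81% | 74% |

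**Sensitivity to hazard shape.** With Weibull shapes from 0.7 to 2.0 and the same 60-month risks, events per 100 patients range from 17.5 down to 13.9. One-sided two-proportion power ranges from 76% down to 66%.

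**The case against.** **Stopping may not end follow-up.** The Statistical analysis section says that, after an early stop for harm or benefit, enrolled participants are still followed for outcomes. One could extend that to the first circumstance and read it as an outer limit on the trial. The end of enrollment is only anticipated, and the sample size may be adjusted after interim looks, so such a limit is not senseless. This stands as an ambiguity, but it does not remove the conflict. The follow-up wording covers only the two early stops. Nor does reading the stop as an end to recruitment fit the stated dates, since recruitment is due to finish about 23 months after it began. If recruitment slips while the rule is read literally, the last entrants lose still more follow-up.

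**The analysis copes with staggered follow-up.** This stands. Under randomization both arms share the same follow-up distribution, so the log-rank comparison is not biased. A reader might infer bias because chi-square and Fisher tests are also named for categorical variables. Crude proportions over 3.1 to 5 years would not estimate a 60-month risk, but that does not bias the between-arm test. Which test is primary is a separate question, and settling it would not repair the stopping rule.

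**Stronger readings that fail.** A reader might infer that the rule pushes power further below 80%. That holds only for a two-sided test. Sidedness is not stated, and the one-sided calculation, which comes closest to the stated 100, starts above 80%. A reader might also say that a planned 60-month comparison becomes impossible. The primary end point is surgical recurrence with no fixed landmark; 60 months appears as the planning horizon. Finally, power computed at 116 complete patients is not the design's power, because the extra 16 are there to absorb loss and leak.

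**Conclusion.** The contradiction is established from the document alone and needs no assumption beyond the stated dates. As written, the rule leaves the last entrants up to 23 months short of the promised follow-up, and almost nobody is observed at the horizon on which the trial was sized. The consequence is lost information, not bias: about 17% fewer events and about 7 to 9 points of log-rank power at 100 patients. Those sizes depend on uniform accrual, constant hazards, 1:1 allocation and no attrition. The absolute power level also depends on sidedness. A hazard that rises over time makes the loss larger, and one that falls makes it smaller.

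**What to change.** Reword the first circumstance under Cessation of trial to: once the last randomized patient has completed 60 months of follow-up after index resection (or has earlier reached surgical recurrence or been lost). On the stated accrual dates this is about 31 December 2025. The cost is one sentence, plus up to 23 months more follow-up for late entrants than the present rule allows. End points already promises that follow-up.

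If the calendar stop has to stay, amend End points to variable follow-up of about 3.1 to 5 years. Then restate the power under Sample size for that follow-up, giving the sidedness and the accrual, hazard and attrition assumptions. On the assumptions above, the two-proportion total for 80% power rises from 98 to 120 one-sided, or from 124 to 152 two-sided, before inflation. Either way, state whether follow-up continues after the first circumstance, as the Statistical analysis section does for the other two.

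### A stop for severe morbidity moves the primary analysis to a mortality end point that the protocol does not define; on annual looks, only one review falls before planned accrual ends

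*Protocol article*

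**What the plan says.** End points, in the protocol article: "The primary end point of the study is postoperative surgical recurrence". Endoscopic and clinical recurrence are secondary. The same section adds that "intra-operative complications and 30-day postoperative outcomes will be evaluated" and lists blood loss, operating time, morbidity, reoperation and length of stay. Death is not listed; it could enter only implicitly, as a Clavien-Dindo grade. The Abstract and the Discussion also give surgical recurrence as primary.

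Statistical analysis sets the schedule: "Interim analyses will be done annually for the first 5 years after index surgery, and the sample size would be adjusted accordingly". It goes on: "An interim analyses will be performed to see if the trial should be continued or stopped, and so it serves as a safeguard". The severe-morbidity rule comes next. If it is met, the trial stops, enrolled participants are still followed for outcomes, and "the primary analysis would have focused on the mortality end point". A stop for benefit instead leads to an analysis of the efficacy end point.

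Cessation of trial lists three circumstances in which the trial stops. The third is that "a clear-cut trend is demonstrated toward increasingly severe morbidity", meaning Clavien-Dindo grade 3 or greater, in either arm. It does not mention follow-up after the stop.

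Trial status: "Trial enrollment began on 1 February 2019 and is anticipated to finish on 31 December 2020".

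**The concern.** The protocol makes the choice of primary end point depend on accumulating safety data, and the replacement is one that it never defines. The switch applies to any morbidity stop, early or late. The replacement also does not match the trigger: grade 3 or greater complications are mostly non-fatal, so a mortality analysis would not measure the harm that stopped the trial. Followed literally, the rule would leave the trial with an uninformative primary result and demote the question it was set up to answer.

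Two related matters bear on how the rule works. The sections differ on what a stop means for follow-up. And annual review suits an outcome that builds up over five years better than one that is complete 30 days after a single operation.

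**Working it through.** **1. End points side by side.**

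| Place | Primary analysis or end point |
|---|---|
| Abstract; End points; Discussion | Surgical recurrence |
| Statistical analysis, general | Intention-to-treat analysis of the primary outcome |
| Statistical analysis, stop for benefit | The efficacy end point |
| Statistical analysis, stop for morbidity | A mortality end point, with no definition, time window or place in End points |

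The last row cannot be reconciled with the others as written.

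**2. What a mortality comparison could show.** The sample size is 116: 100 × 1.10 × 1.05 = 115.5, which matches the stated allowance for loss to follow-up and leak. Take 58 per arm. With Fisher's exact test, which the protocol names, and all deaths in one arm:

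- 5 v 0: 2 × (58·57·56·55·54)/(116·115·114·113·112) = 2 × 0.0286 = 0.057
- 6 v 0: 2 × 0.0286 × 53/111 = 0.027

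At least six deaths to none are needed for P ≤ 0.05, which is 6/58 = 10% mortality in one arm. The documents give no mortality rate. If it were 1% to 2% (assumption), the expected total is 116 × 0.01 = 1.2 to 116 × 0.02 = 2.3 deaths. A stop before full accrual would leave fewer patients still.

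**3. What a stop means.** Statistical analysis says that enrolled participants are followed after a morbidity stop. Cessation of trial puts the morbidity stop in the same list as reaching five years from first enrollment, which is the end of the trial itself. Read alone, that section can be taken to end follow-up.

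**4. Timing of the annual looks (secondary point).** Assume uniform accrual and looks counted from the first operation, at or soon after 1 February 2019.

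- Accrual window, 1 February 2019 to 31 December 2020: 700 days, or 23.0 months.
- Look 1, about 1 February 2020: operated 116 × 365/700 = 60; with 30-day data 116 × 335/700 = 56; still to be operated 116 − 60 = 56.
- Last 30-day window closes 30 January 2021.
- Look 2, about 1 February 2021: 32 days after planned close, with all 116 operated and all 30-day data complete.
- Looks 3 to 5 add no 30-day morbidity data.

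If each look instead waits until every patient is one year past surgery, none falls within accrual.

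**5. Size of the secondary point.** The documents give neither a grade 3+ rate nor a numerical trigger, so all rates below are assumptions. The trigger is z = (p_E − p_L)/√[2p̄(1 − p̄)/n] at or above a fixed value, with n patients per arm having 30-day data. One look at 56 patients uses z ≥ 1.645. Three looks at about 30, 56 and 86 patients use z ≥ 1.85. At 10% v 10% both give false alarms of about 5% to 6%. Exposure counts patients already operated, including those awaiting 30-day data (116 × 30/700 ÷ 2 = 2.5 per arm at a look). Results are from simulation.

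| Assumed grade 3+ rate, limited v extensive | Flagged: three looks v one | Mean extensive-arm patients operated (of 58): three looks v one |
|---|---|---|
| 10% v 20% | 36% v 29% | 49 v 50 |
| 10% v 25% | 57% v 46% | 42–43 v 45 |
| 10% v 30% | 75–76% v 62% | 36–37 v 41 |

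Ranges show the spread between repeated simulation runs.

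**The case against.** The strongest objection is to the timing point. Cessation of trial does not tie the morbidity criterion to the annual looks. Statistical analysis also has the treating clinicians and an external committee monitoring data, and the Discussion promises close watching of complications. This is a condensed article, so review frequency and numerical triggers may sit in the full protocol or a committee charter. That stands: a missing threshold is no finding here, and the timing point is conditional. Annual review is still the natural reading, because the morbidity rule directly follows the sentences that set the annual analyses and call the interim analysis the safeguard.

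Three stronger readings are tempting, and the documents do not support them.

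- *A trigger after the first look protects nobody.* Too absolute. Randomization allows delayed resection with re-randomization at six months, the sample size may be adjusted, and look 2 falls only 32 days after an anticipated close. Few or none under the planned dates is the most that can be said.
- *A late trigger destroys the recurrence data.* Statistical analysis keeps enrolled participants under follow-up. The damage comes from the end-point switch, and that does not depend on when the trial stops.
- *Extra looks raise detection from 46% to 67% at 10% v 25%.* That holds only if all three looks use the unadjusted z ≥ 1.645, which lifts false alarms from about 6% to 10%. At matched false alarms the gain is to 57%.

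On the main point, one could argue that mortality is a drafting slip, perhaps for morbidity. That may be so, but the document does not say it, and morbidity as primary would equally displace surgical recurrence.

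**Conclusion.** The main point holds on the text alone. After a morbidity stop the protocol replaces its primary end point with one that it neither lists nor defines, and a trial of this size is unlikely to learn anything from it. That deaths will be few is a judgement from the age range and sample size; the six-to-none requirement assumes 58 per arm. The two sections also need to agree on whether a morbidity stop leaves follow-up in place.

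The timing point holds in a limited form. If review is annual from the first operation and accrual runs to plan, only one look, with about 56 of 116 patients evaluable, can influence who is operated. More frequent review brings a moderate gain in detection (7 to 14 percentage points across the assumed rates) and a small saving in exposure (about one to five extensive-arm patients).

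**What to change.** 1. In Statistical analysis, replace the mortality clause with a statement that surgical recurrence by intention to treat remains the primary analysis however the trial ends, and that deaths and grade 3 or greater morbidity are reported by arm as safety outcomes. This costs one sentence.
2. Reconcile Statistical analysis with Cessation of trial, so that both say a morbidity stop ends recruitment while follow-up for recurrence continues. This costs one sentence.
3. Preferably, have the existing external committee see 30-day grade 3+ counts by arm more often during accrual, for example at about 30, 56 and 86 patients with 30-day data, with a review trigger fixed before the first look and set to hold false alarms at the intended level. This costs two extra safety tables. If the full protocol or a charter already provides for it, a cross-reference is enough.
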